### Trial management

The chief investigator has ultimate responsibility for the trial management, assisted by the trial management group. Any important protocol modifications will be communicated to all relevant parties (investigators, research ethics committee, NIHR CRN Portfolio, trial registry, journals, NHS Research and Development, device manufacturer, funding body) by the chief investigator.

A trial steering committee has been established, which will also act as a data monitoring committee. In addition to annual meetings, the committee will be issued with information about any adverse events throughout the course of the study, so that they can decide whether it is appropriate for the study to be terminated. A 3-monthly newsletter will be issued to all investigators and the steering committee, updating on recruitment and other issues, throughout the trial.

### Safety monitoring

All adverse events (AEs) and serious adverse events (SAEs) will be recorded. The chief investigator (AB) will be provided with an update of AEs every month and all SAEs within two working days. This trial does not involve a medicinal product or life-threatening procedure. Hence, the risk of a SAE is low. However, one potential SAE is an increased rate of progression to nAMD in the eye with early AMD at baseline. Although this is at odds with the literature, it is not an impossible outcome. Another potential SAE would be an increased rate of recurrence of nAMD in the fellow eye (resulting in increased ranibizumab retreatment rates). Conversion to nAMD and Ranibizumab retreatment requirement in the fellow eye will be determined by ophthalmologists at the monthly ranibizumab clinic, and recorded by the study investigator through assessment of medical records after each monthly ranibizumab appointment.

Wong et al. [52] carried out a meta-analysis of studies, which had looked at the progression to choroidal neovascularization in the fellow eye when free of advanced disease at study inception. They reported that the cumulative 1-year incidence of nAMD in the 426 patients enrolled in the five studies that evaluated this outcome was 12.2% (confidence interval, 1.7% to 30.6%). Therefore, we have placed an upper limit on the number of people expected to convert to nAMD per month of *n* × (30.6% / 12 months), where *n* is the number of people in the trial who are using the light therapy light mask.

The chief investigator will assess the nature of the AEs and SAEs for seriousness, causality and expectedness. Following the initial report, follow-up data may be requested by the chief investigator. Where the SAE is both related and unexpected, the chief investigator will notify the Trial Steering Committee, the trial sponsor, the National Research Ethics Service North West, and the device manufacturer, who will notify the Medicines and Healthcare Regulatory Agency within 15 days of receiving notification of the SAE.

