### Recruitment

Sixty participants will be recruited to the trial. Ophthalmologists will identify potential trial participants who are attending for their first appointment at the nAMD clinic at Bristol Eye Hospital, and will provide them with an information sheet and ask for their permission to be contacted by the study investigators. The potential participants will be contacted at least 2 days after their receipt of the information sheet, and invited to meet the study investigator at their next visit to the nAMD clinic (approximately 1 month later) to discuss the trial, provide consent if they choose to participate, and carry out some basic screening tests. Participants will be informed after this screening visit whether they are eligible to take part in the study. Owing to the low number of patients required to participate in the study it is planned for the trial and data collection to take place principally at a single NHS centre, that is, the Bristol Eye Hospital. If needed, additional participants will be recruited from supplementary recruitment centres to ensure that targets are met.

Forty control participants and participants with grade 1 AMD (AREDS simplified scale [45]) for the baseline cross-sectional analysis will be recruited by local optometrists in Bristol and Cardiff, from a database of elderly volunteers, from the Bristol Eye Hospital, from the list of research volunteers at the Cardiff University Eye Clinic and from staff and students of Cardiff University.

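### The monthly limit on conversions in the mask arm is below one person, so a single background conversion exceeds it and the limit cannot tell harm from the expected rate

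*Protocol article*

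**What the plan says.** The protocol article, under Safety monitoring, takes its background rate from a meta-analysis of fellow eyes free of advanced disease at study entry. It gives a one-year cumulative incidence of neovascular AMD of 12.2%, with an interval running from 1.7% up to 30.6%. From the upper end of that interval it derives a limit. The sentence opens "Therefore, we have placed an upper limit on the number of people expected to convert to nAMD per month of", and the formula that completes it multiplies n by one twelfth of 30.6%. The symbol n covers the mask arm alone, since it "is the number of people in the trial who are using the light therapy light mask".

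The size of the mask arm follows from two other sections. Recruitment states: "Sixty participants will be recruited to the trial". Randomization gives a 1:1 allocation. Statistical methods allows for 15% dropout, leaving 51 in total, and rules out an interim analysis. Interventions says that a participant whose early-AMD eye converts is withdrawn. The article states no numerical value for the limit, no rounding rule and no false-alarm or detection probability.

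**The concern.** The authors evidently meant to be lenient, since they used the upper confidence bound (30.6%) rather than the point estimate (12.2%). But they divided an annual proportion by 12 and applied it to an arm of about 30. That gives a limit smaller than one person, while conversions are whole numbers: zero is within the limit and one is over it. The leniency is lost.

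This matters because safety in AMD is a stated main aim, Eligibility criteria gives conversion in the test eye as an example of a serious adverse event, and this formula is the only numerical safety limit in the article. The steering committee, which also acts as data monitoring committee, is to judge from adverse-event information whether the trial should end. A limit that background events exceed almost surely gives it no usable signal.

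**Working it through.** **Inputs.** Annual background incidence 12.2% and upper bound 30.6% (Safety monitoring). 60 randomised 1:1, so n ≈ 30 (Recruitment, Randomization). After 15% dropout, 51 in total, so about 26 in the mask arm (Statistical methods). A second background figure of about 10% per year for all advanced AMD (Outcome measures). The doubled rate, 2 × 12.2% = 24.4%, is my assumption, used only as a benchmark for harm.

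**Step 1: value of the limit.** The article prints only the formula, so there is no stated figure to reproduce. Per user the limit is 30.6% / 12 = 2.55% per month.

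| n using the mask | limit per month |
|---|---|
| 15 | 0.38 |
| 26 | 0.66 |
| 30 | 0.77 |
| 39 | 0.99 |
| 40 | 1.02 |

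The limit reaches 1 at n = 12 / 0.306 = 39.2, that is, at 40 users. Sixty people randomised 1:1 in permuted blocks cannot plausibly give 40. Staggered recruitment, dropout and withdrawal on conversion all push n downwards.

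**Step 2: chance of exceeding it in one month, no harm.** Monthly risk = 1 − (1 − 0.122)^(1/12) = 1.08%. With 30 users, P(at least one conversion) = 1 − (1 − 0.0108)^30 = 27.8%. The expected number is 30 × 0.122 / 12 = 0.305 per month, or 3.66 per year.

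**Step 3: chance of exceeding it at least once in 12 months.** Any single conversion is enough, so this is 1 − (1 − p)^n.

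| annual rate | n = 30 | n = 26 |
|---|---|---|
| 10% | 95.8% | 93.5% |
| 12.2% (background) | 98.0% | 96.6% |
| 24.4% (doubled) | 99.98% | 99.93% |

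At n = 30 the step from no harm to doubled risk moves the probability from 98.0% to 99.98%. In a simulation of 10,000 trials with converters removed, the mean number of months over the limit was 3.2 of 12 at 12.2% and 5.5 of 12 at 24.4%. That frequency carries some information, but the article does not use it.

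**Step 4: the accumulated reading.** Twelve monthly limits at n = 30 add up to 12 × 0.765 = 9.18, so 10 or more conversions would exceed the total. Binomial(30, p) gives P(X ≥ 10) = 0.2% at 12.2%, 17.5% at 24.4% and 44% at 30.6%. False alarms almost vanish, but a doubled rate would usually go unnoticed.

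**The case against.** The strongest reply concerns how the limit is read. The text speaks of a number expected per month. It does not call this a stopping rule and attaches no action to it. A monthly quantity can be a rate to be accumulated, in which case the whole-number problem disappears. This stands in part: the wording is open to that reading, although the month-by-month one is more literal. But step 4 shows that the accumulated version fails in the opposite direction. Rounding the monthly limit up to one, which the text does not mention, would not help much either. In the simulation at n = 30, two or more conversions in some month occurred in 38% of trials at 12.2%, against 82% at 24.4%.

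A second reply is that a journal article may leave operating characteristics and the action on breach to the full protocol. That is fair, and their absence is not the point here. The point is the formula and time unit that are printed.

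Third, monitoring is wider than the formula. Data collection methods has conversions followed monthly in both arms, and Trial management says that "the committee will be issued with information about any adverse events throughout the course of the study". This stands. The control arm is missing from the limit, not from the monitoring.

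A reader might infer several stronger points that the documents do not support:

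- **That the limit cannot detect harm.** It is exceeded almost surely under harm. What it lacks is specificity.
- **That the reporting routes conflict.** Safety monitoring says: "Where the SAE is both related and unexpected, the chief investigator will notify the Trial Steering Committee". Trial management promises information on any adverse event. These can be expedited and routine channels, and Safety monitoring does not say that only related and unexpected events reach the committee.
- **That people who stop the mask drop out of n.** Using the mask may simply mean allocated to it, and the text does not settle this.

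**Conclusion.** The point holds. Read as written, the limit is about 0.77 people per month, and every month with a conversion is over it. At the article's own background rate that happens in 28% of months and at least once in 12 months with probability 98%, against 99.98% at a doubled rate. The limit therefore cannot distinguish harm from background. Accumulated over 12 months it would be exceeded only 17.5% of the time at the doubled rate, so neither reading gives a useful safeguard.

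The probabilities assume 30 mask users followed for 12 months, independent conversions and a constant risk over the year. The conclusion is not sensitive to these: with 26 users the 12-month figure is still 96.6%, and with the 10% rate and 30 users it is 95.8%. Staggered entry lowers the chance in any one calendar month. It does not alter the chance of at least one conversion across the arm if each person completes 12 months.

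**What to change.** Replace the per-month formula with a cumulative count of conversions per person-time among everyone randomised to the mask. Compare it with the number expected from the cited background incidence and with the concurrent control arm. Choose the threshold from a short table of its false-alarm probability at the background rate and its detection probability at raised rates, calculated under the planned staggered recruitment, 15% dropout and withdrawal on conversion. Changing the time unit alone is not enough, because step 4 shows that a limit built on 30.6% has little power against a doubled rate.

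The threshold, and what follows when it is crossed, are for the sponsor and the steering/data monitoring committee to set.

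The cost is one paragraph of protocol text and a small calculation. Conversions are already recorded monthly in both arms, so no new data are needed.

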### Data management

Any trial data will be recorded on spreadsheets using the numerical identifier for each patient. These data will be non-identifiable. All paper records will also use the unique numerical identifier, which will be non-identifiable. The only identifiable personal data will be the paper and electronic copies of the patient database. The paper copy will not be transferred between Cardiff University and the Bristol Eye Hospital, and will be kept in a locked filing cabinet at all times. The electronic database will be stored on a secure Cardiff University computer drive, which is accessible from Bristol and Cardiff via a password-protected connection. The study database will be checked for integrity every month by the chief investigator. At the end of the trial, the data will belong to Cardiff University. At this time, Polyphotonix Medical Ltd (the manufacturer) will have access to the results. Anonymized data will be available for verification at any time by the funding body, the College of Optometrists, on request. Neither the College of Optometrists, nor Polyphotonix Medical Ltd. will influence the data collection or analysis. All data will be kept for 15 years, in line with Cardiff University’s Research Governance Framework Regulations for clinical research.

### Dissemination

A summary of the trial protocol is available to the public through the International Standard Randomised Controlled Trials Register. Any interested individuals may contact the chief investigator for further information. Results will be published in peer-reviewed journals and at International Conferences. The chief investigator has ultimate responsibility for the scientific content of any publications. Dissemination of results to trial participants will take place through a summary-of-findings newsletter sent at the end of the trial to those individuals who indicate a desire to receive an update. Dissemination to the wider community of people with AMD will take place through publication in the Macular Society’s members’ magazine, *Digest*, and through presentations at such events as the Macular Society ‘Top Doctors’ conference. Neither the funding body (the College of Optometrists), the light mask manufacturer (Polyphotonix Medical Ltd), nor the sponsor (Cardiff University) will influence the presentation or the publication of the research.

### Ethical considerations

The study has been approved by the National Research Ethics Service North West, and is registered with the International Standard Randomised Clinical Trials Register. A notice of no objection has been obtained from the Medicines and Healthcare Regulatory Agency. The trial will be conducted in adherence with the Declaration of Helsinki and the Good Clinical Practice guidelines. The chief investigator and the research team will preserve the confidentiality of participants in accordance with the Data Protection Act 1998.

### Audits and inspections

The trial is liable to inspection by the College of Optometrists as the funding organization. The study may also be liable to inspection and audit by Cardiff University under their remit as sponsor.

## Discussion

In this article, we present a clinical trial protocol to evaluate the effect of low-level night-time light therapy in patients with early AMD. To our knowledge, this is the first randomized controlled trial of its kind in AMD. This study will provide the foundation for future large-scale clinical trials. With the prediction of longer life expectancy in the future, the prevalence of AMD and its associated social and economic problems will continue to increase unless a treatment is developed that will stop its progression.

## Trial status

This protocol aims to establish the therapeutic benefit of low-level light therapy on disease progression in AMD. Recruitment will begin in April 2014 and continue until February 2015. Data collection will take place from June 2014 to April 2016.

## Abbreviations

AE: adverse event; AMD: age-related macular degeneration; ANCOVA: analysis of covariance; ANOVA: analysis of variance; AREDS: age-related eye disease scale; CE: Conformité Européenne; ETDRS: Early Treatment of Diabetic Retinopathy Study; nAMD: neovascular age-related macular degeneration; OCT: optical coherence tomography; PSQI: Pittsburgh Sleep Quality Index; SAE: serious adverse event; VALVVFQ-48: 48-item Veterans Affairs Low-Vision Visual Functioning Questionnaire.
